### Ethical considerations

The protocol received the approval of the Comité de Protection des Personnes (Commission for Public Safety) SUD-EST VI of Clermont-Ferrand on March 5th, 2010. The study is conducted in compliance with the regulations on patient confidentiality (Comité consultatif sur le traitement de l’information en matière de recherche dans le domaine de la Santé (Advisory Committee on Data Processing for Matters of Research in the Field of Healthcare) and Commission Nationale de l’Information et des Libertés (National Commission for Data Protection) agreements). Inclusion is voluntary and subject to strict anonymity and medical confidentiality. The description of this design follows the CONSORT recommendations for reporting on trials (http://www.consort-statement.org). The trial has been registered on http://clinicaltrials.gov/: NCT01433692.

## Discussion

The main assessment criterion being consumption by amount of joints smoked in each group, it is difficult to establish a quantity of consumption for cannabis (e.g., shared joints, joints that are more or less 'concentrated’). The epidemiologic data usually quantifies consumption by 'use’ of cannabis: that is to say 'the amount of times that the adolescent has smoked’ [1,3,4]. Concordances were established; half of recent smokers smoke one or less than one joint per use, and 70% of them smoke two or less. Regular or occasional smokers smoke five joints or more per use in 30% of cases [4]. It would have been possible to assess consumption more objectively using biological sampling (hair samples, urine tests). However, early treatment in general medicine requires a relationship of trust between the doctor and the patient; mandatory biological testing would have been badly received by adolescents. The CAST score (Cannabis Abuse Screening Test) is only assessed at the start of the study, as it has the sole objective of detecting problematic use of cannabis [28,29], but is not suited to measuring the progression of consumption. It will enable comparison of the progression of consumption in adolescents who had an initial score which revealed harmful use and the others. The primary and secondary criteria are collected during the preceding month, then at 3, 6, and 12 months. Collection during the preceding month was chosen in order to limit memorization bias, while maintaining a sense of overall consumption, as certain patients do not consume cannabis regularly.

Any adolescents who consume cannabis are eligible, on the condition that they smoke at least one joint per month. These levels of consumption may appear highly dispersed, but the European School Survey Project on Alcohol and other Drugs and the Survey on Health and Consumption administered during the Defence Preparation Day data described correlations between quantity consumed and certain behaviours (without causal links to date), e.g., runaways, school absenteeism, depression, and acts of violence. The difference in behaviour between occasional and regular consumers is less significant than between occasional consumers and non-consumers [18]. These consumers thus constitute a homogeneous group as regards behaviour. The selection of the 15–25 age bracket appears to be relevant for carrying out a trial on intervention on cannabis consumption. Fifteen years of age is the average age of experimentation with cannabis, and 25 years of age is the apex of consumption [2]. Consumption is quite homogeneous; in the 19–25 age bracket, 14.6% are repeat consumers [2], and in 12–19 year olds, 16.4% are repeat consumers [3].

The participation of GPs in a study depends mainly on the applicability of the topic to their practice, remuneration, the support of the study coordinators, and the feedback of information [30]. Lack of time and the administrative burden are the main obstacles to the inclusion and follow-up of patients by the GP [31]. The illegal aspect of cannabis consumption in France can also present an obstacle to the recruitment of GP investigators and the inclusion of adolescents. The Scientific Committee of CANABIC developed a strategy relating to doctors and patients in order to optimize inclusion [25-31]: GPs are remunerated, the CRFs can be completed quickly and reattempts are carried out by the regional coordinators. A pilot study tested the feasibility of the study among volunteer GPs. Analysis of the difficulties encountered by the investigators made it possible to optimize certain features of the protocol through extension of the inclusion period (12 months) and the absence of any specific qualification in addiction treatment of the investigators. It does indeed appear that when the practitioners have such a qualification, they already apply these specific interview techniques and the training day has little impact on them. In order to strengthen the participation of patients, they were sensitized to the danger of cannabis to their own health and were empowered, through the various stages of the BI [25].

There is currently broad consensus deeming that it is important to identify at an early stage potentially addictive behaviours in adolescents, as on the one hand progression towards cannabis dependency partly depends on the age at which consumption begins [32], and on the other primary prevention actions have not, to date, demonstrated the effectiveness expected [33]. In several studies, the BI appears to be a relevant tool in terms of acceptability and feasibility among cannabis-using adolescents [12-15]. A trial that does not demonstrate effectiveness raises the question of the homogeneity of the BI carried out [34]. Recent trials have shown promise regarding the impact at 6 months of a BI carried out for the consumption of several drugs [35,36]. Solid evidence of the effectiveness of a BI on the reduction in cannabis consumption remains to be found, particularly when it is carried out by GPs. Easily accessible through ongoing or initial training, the BI should improve the overall care provided to adolescents who consume cannabis and are monitored in primary care.

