## Methods

The main assessment criterion is the amount of joints consumed per month at the 12^th^ month following the inclusion consultation. In the absence of consensus on the definition of a threshold for dangerous cannabis consumption, it is impossible to refer to a target level of consumption. In the light of epidemiological data (proportions of recent, repeated, regular, and daily users in the age group 15–25 years) [1,2], we considered that cannabis users consumed an average of 15 joints per month. Our working hypothesis is that the intervention will result in a 30% reduction in the stated consumption of cannabis at 12 months (that is to say five joints per month). The Hawthorne effect [24] was taken into account by estimating that adolescents of the control group would reduce their consumption by 15% (i.e., two joints per month).

A difference of 30% between the intervention group (i.e., three joints per month) and the control group appears to be clinically relevant.

Some secondary hypotheses are reported in case report forms (CRFs) at 3, 6, and 12 months by the GP: the change to other methods of cannabis consumption such as consumption by “bong” or “water pipe” and the impact of the change in cannabis use on tobacco and alcohol consumption.

Other secondary hypotheses are collected by a declaratory self-administered questionnaire completed by the patient at the start and end of the study: how it is consumed (alone or with friends, weekday or weekend, joints or bongs), changing perceptions of the danger of consumption for health, and driving after smoking.

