### Inclusion and non-inclusion criteria

#### Inclusion criteria

All young persons from 15 to 25 years of age consuming at least one joint per month for at least one year and registered with a social security scheme are eligible for the study (as stated in the law: Code of Public Health. Article L1121_11*).*

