### Randomization

The doctor’s surgery is the unit of randomization. Patients of an investigator GP are assigned to the same group as him/her. Investigators from the same doctor’s surgery are randomized within the same group in order to avoid contamination bias. As the study is being carried out in three regions in which behaviours in terms of cannabis consumption and sociodemographic parameters may differ, the randomization is stratified by region and by state and is carried out using Stata, version 12 (StataCorp, College Station, USA). Taking into account the risk of contamination generated by adolescents who discuss the study with their peers while their doctors belong to different groups, collection of the name of the school/college and the class is planned in order to evaluate the possible impact of interpenetration. The same will apply for registration with one or several associations (patients were asked about their membership in a sports or cultural association; data was collected by GP during consultation).

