#### Statistical analyses

All data will be entered into a customized Access database (Microsoft, Redmond, Wash, USA). Analyses will be performed using Stata, version 12. All data will be analyzed by intention to treat. The tests were two-sided, with a type I error set at α = 0.05 (except for multiple comparisons when appropriate). Baseline characteristics (GPs and their patients) will be presented as the mean ± standard deviation (SD) or the median (interquartile range) for each randomization group for continuous data and as the number of patients and associated percentages for categorical parameters. Hierarchical linear regression models (mixed models) with levels for practice, individuals within practices, and repeated measurements per individual have been used to estimate effects of the intervention on number of joints smoked per month post-baseline time points. These models (intercept and slope as random effects) included an interaction between randomization group and time point, and adjusted for number of joints smoked per month at baseline, age of first consumption, gender, CAST at baseline, socioeconomic status, and GP’s characteristics. Intraclass correlation coefficients are presented by arm. The secondary analyses will compare changes on between groups with random effects models: method of consumption, supply method, perception of the effects on health, professional life, social life, and driving under the influence of alcohol will be also compared. This data will be collected through a self-administered questionnaire that the patient will complete and leave at the GP’s surgery. To assess the problem caused by missing data (GP and patients), estimation methods developed by Verbeke and Molenberg are proposed.

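### The primary model's covariate list leaves out age at inclusion, which must be established for every patient and could differ between arms because GPs recruit after allocation

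*Protocol article*

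**What the plan says.** **Eligibility** (Protocol article, Inclusion criteria): "All young persons from 15 to 25 years of age consuming at least one joint per month for at least one year". A GP therefore has to establish current age before including anyone. Duration of use is one of the three screening questions under Recruitment.

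**Endpoint** (Methods): "The main assessment criterion is the amount of joints consumed per month at the 12"th month after inclusion.

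**Primary model** (Statistical analyses): a mixed model, "adjusted for number of joints smoked per month at baseline, age of first consumption, gender, CAST at baseline, socioeconomic status, and GP’s characteristics". Current age is not listed.

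**Allocation** (Randomization): "The doctor’s surgery is the unit of randomization". Stratification is on region and state, not age. Under Recruitment, each GP enrols the first five eligible adolescents seen, and intervention GPs deliver the brief intervention at that same consultation.

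**Age range** (Discussion): "Fifteen years of age is the average age of experimentation with cannabis, and 25 years of age is the apex of consumption", followed by "Consumption is quite homogeneous; in the 19–25 age bracket, 14.6% are repeat consumers [2], and in 12–19 year olds, 16.4% are repeat consumers".

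**The concern.** The covariate list is explicit, so the absence of current age is a choice made in the article and not a detail left to another document. Age at first use is in the model and age now is not. The one remark that might make current age look unimportant is the Discussion's claim of homogeneous consumption, and the figures given for it concern neither the enrolled ages nor the endpoint.

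Two things are at stake. The first is some precision, if age predicts month-12 consumption beyond the covariates already listed. The second comes from the cluster design. Intervention GPs have had a training day on raising the subject with adolescents and know their arm when they decide whom to ask. The age mix they recruit could therefore differ from that of control GPs for reasons other than chance. Randomizing surgeries does not protect against this; adjusting for age would do so in part.

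**Working it through.** **1. The homogeneity figures.** The shares of repeat users are 16.4% at 12–19 and 14.6% at 19–25. The difference is 16.4 − 14.6 = 1.8 points and the ratio 14.6/16.4 = 0.89. Set against the trial:
- The younger band contains ages 12, 13 and 14, which are ineligible, and the bands overlap at 19.
- The figures are shares of people in a use category, while the endpoint is joints per month among users. If the Discussion uses the Background's definition of repeated use, that category alone runs from 10 uses a year to 10 a month (10 × 12 = 120 a year) and leaves out regular and daily users. Similar shares are compatible with very different amounts.
- The older band has the lower share, which sits awkwardly beside an apex at 25.

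**2. Whether age of first consumption can stand in for current age.** Entry requires at least a year of use. A 16-year-old can have started no later than about 15, a 25-year-old as late as 24. Age at onset is thus partly tied to current age by the entry rule, and its coefficient mixes onset with current age and duration. With both ages in the model, duration is accounted for as well.

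**3. Precision.** Let r be the partial correlation of age with the outcome given the listed covariates. The documents give no value, so a range is assumed. The variance with age omitted, relative to age included, is 1/(1 − r²) when age varies mainly within clusters:

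| r (assumed) | 1/(1 − r²) | cost |
|---|---|---|
| 0.1 | 1.010 | 1% |
| 0.2 | 1.042 | 4% |
| 0.3 | 1.099 | 10% |

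**4. Chance imbalance in age.** From the article, 25 GPs × 5 patients = 125 per arm per region, and 3 × 125 = 375 per arm overall. Assumed: age SD 3 years (a uniform spread over 15–25 would give 10/√12 = 2.9) and an ICC of age from 0 to 0.2. The SE of the between-arm difference in mean age is 3 × √[(2/n)(1 + 4 × ICC)]:
- one region, n = 125: 0.38 (ICC 0), 0.45 (0.1), 0.51 (0.2) year
- overall, n = 375: 0.22, 0.26, 0.29 year

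This is not bias. It is already part of the SE of the treatment difference. At the largest SD and ICC in Sample size estimation (5 and 0.2), before dropout, that SE is 5 × √(2 × 1.8/125) = 0.85 joint in one region and 5 × √(2 × 1.8/375) = 0.49 overall.

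**5. Systematic imbalance from recruitment.** Shift in the estimate = residual slope × age difference. With an assumed slope of 0.1 to 0.5 joint per month per year of age and an assumed difference of 0.5 to 1 year, the shift is 0.1 × 0.5 = 0.05 to 0.5 × 1 = 0.5 joint. The target is three joints as stated in Methods, or (0.30 − 0.15) × 15 = 2.25 unrounded. Neither assumed input has support in the article, so this shows scale only.

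**The case against.** Choosing covariates is a matter of judgement, and this list is prespecified and reasonable. It contains baseline joints and baseline CAST, which carry much of any age difference in level. Omitting a baseline covariate does not bias a randomized comparison in expectation. Enrolling the first five eligible patients also limits the GP's discretion. All of this stands, and it is why the point is small. What it does not answer is recruitment after allocation: the eligible patients a GP finds depend on whom the GP asks.

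Three stronger readings are tempting and not supported:

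- **That the Discussion contradicts itself.** Fifteen is given as the average age of experimentation, not as the start of use for everyone. A population peak at 25 does not describe how an existing user's consumption changes over 12 months. Neither statement is strictly incompatible with similar shares of repeat users.
- **That a 16-year-old and a 25-year-old who both began at 15 are treated as alike.** They are so only if they also match on baseline joints, CAST, gender, socioeconomic status and GP characteristics.
- **That age imbalance would move a regional result by 10% to 20% of the effect.** Such a figure needs a slope of 0.25 to 0.5 joint per year, which the article does not support, and a 1.96-SE chance imbalance (1.96 × 0.45 × 0.25 to 0.5 = 0.22 to 0.44 joint, over 2.25). Those shifts lie well inside the 0.85-joint regional SE and are already counted in it.

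**Conclusion.** The point holds as a small, free improvement. Current age is missing from a stated covariate list and from the stratification, and the homogeneity figures do not show that it is unimportant for joints per month at ages 15–25. The expected gain is about 1% to 10% in variance, resting on an assumed partial correlation of 0.1 to 0.3. Adjustment would also give some protection if recruitment after allocation makes the arms differ in age; the article gives no basis for putting a size on that. The primary analysis remains valid without the change, and the 250 patients per region are unaffected.

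That age is available for every patient is an inference from the eligibility rule; the article does not say so directly.

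**What to change.** In Statistical analyses, add age at inclusion, as a continuous variable, to the covariates of the primary mixed model, and keep age of first consumption. This should be settled before outcome data are examined by arm. The cost is one degree of freedom and no new data collection, given that age is checked at inclusion.

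As an editorial matter only, the Discussion could say that the quoted shares describe repeat use in bands that do not match the enrolled range, and drop the statement that consumption is homogeneous. That changes nothing in the design or the estimate.

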## Trial status

The CANABIC study is ongoing.

## Abbreviations

BI: Brief intervention; CAST: Cannabis abuse screening trial; CG: Control group; FRAMES: Feedback, Responsibility, Advice, Menu, Empathy, Self-efficacy; CRF: Case report form; GP: General practitioner; IG: Intervention group; MI: Motivational interviewing.
